## Abstract

**Background:**

This paper describes the rationale and design of the RECOVER study. Currently, there is no consensus regarding the optimal treatment for high-risk, non-metastatic prostate cancer (PCa). The study primarily aims to evaluate and compare the impact of treatment with robot-assisted radical prostatectomy (RP) versus external beam radiation therapy (EBRT) with androgen deprivation therapy (ADT) for men with high-risk, non-metastatic PCa regarding health-related quality of life (HRQoL) and functional outcomes. Secondary objectives are progression-free survival (PFS), distant metastasis-free survival (DMFS), costs and cost-effectiveness.

**Methods:**

The RECOVER study is a comparative effectiveness study that prospectively includes newly diagnosed high-risk (cT3a-bN0M0, ISUP-grade ≥ 4 and/or PSA > 20 ng/mL), non-metastatic PCa patients. Four Dutch prostate cancer networks, comprising 29 hospitals, are currently participating in the study. Patient reported outcomes are collected before treatment initiation, 12 months and 36 months after treatment initiation and include the EORTC-QLQ-C30, the EPIC-26, an adapted version of the SCQ, an adapted version of the iMTA Productivity Cost Questionnaire and several specific questions regarding patient characteristics, treatment of PCa specific complaints and health resources used. Clinical data regarding patient-, tumor- and treatment characteristics and oncological outcomes are collected up to 5 years after diagnosis. For sufficient power, patient reported outcomes of 471 patients must be collected 36 months after treatment initiation. Descriptive statistics and mixed-effects models are used to assess differences in HRQoL and functional outcomes over time between the patients treated with radical prostatectomy versus EBRT (+ ADT). Inverse probability of treatment weighting or the g-formula are used to adjust for confounding covariates associated with treatment. Secondary endpoints PFS and DMFS are evaluated using a competing risk analysis and cost-utility and budget-impact analyses will be performed to determine cost and cost-effectiveness.

**Discussion:**

An observational prospective design was chosen since a randomized controlled trial comparing surgery and radiotherapy was not deemed feasible. This study evaluates effectiveness of treatment in a routine clinical setting (with adjustment for confounding) and its findings will enhance patients’ and healthcare professionals’ awareness for the impact of both treatment modalities on (long-term) daily functioning and HRQoL and aid treatment decision making.

**Trial registration:**

This study is registered at ClinicalTrials.gov (NCT05931419).

## Background

Approximately 15–18% of all prostate cancer diagnoses concern high-risk, non-metastatic prostate cancer (PCa) [1–3]. High-risk PCa is a heterogenous disease with increased risk of biochemical recurrence, metastatic progression and death from PCa as compared to low- or intermediate-risk localized disease [4–6]. Treatment modalities widely used for high-risk PCa are (robot-assisted) radical prostatectomy (RP) and external beam radiation therapy (EBRT), the latter generally combined with androgen deprivation therapy (ADT). Currently, there is no consensus regarding the optimal treatment for high-risk PCa [7]. This is also reflected in the substantial interhospital treatment variation in the Netherlands [8].

High-level comparative evidence regarding the optimal treatment for high-risk PCa is lacking. Several non-randomized studies have compared oncological outcomes between treatment with RP versus EBRT. Most were retrospective in nature and were performed in a single-institution. These studies did not show clear differences in five-year prostate cancer specific survival (PCSS) and overall survival (OS) [9–14]. Due to variation in the definition of high-risk prostate cancer and differences in applied surgical and radiotherapy treatment strategies, definitive conclusions cannot be drawn [9]. However, survival was generally good with reported five-year OS and PCSS rates exceeding 90% [9–14]. In a recent systematic review we summarized evidence for patient reported functional outcomes and HRQoL after RP compared to EBRT for high-risk, non-metastatic PCa [9]. Three observational studies focused on differences in functional outcomes and HRQoL between RP and EBRT with ADT for high-risk PCa. Overall, sexual dysfunction and genitourinary toxicity were reported more often after RP, while reduced hormonal function and gastro-intestinal toxicity were more common after EBRT combined with ADT [12, 15, 16]. However, due to the limited number of studies, the variation in the definition of high-risk PCa and the differences in methods and measurement instruments, the extent of the effect of both treatment modalities on functional outcomes and HRQoL remains largely unknown. Hence, it remains uncertain whether either treatment is superior with respect to functional outcomes and HRQoL as well as oncological outcomes.

Here we present the RECOVER study (High-Risk prostatE Cancer radiatiOn Versus surgERy) as a means to address these knowledge gaps. The study is primarily designed to evaluate and compare the impact of treatment with RP versus EBRT with ADT on functional outcomes and HRQoL for men with high-risk, non-metastatic PCa. Our study aims to enhance awareness of both patients and healthcare professionals regarding these effects of treatment. By incorporating our findings into a patient decision aid, it could support patients in making a well-informed treatment decision. Moreover, providing insight into the impact of both treatments could lead to a reduction in interhospital and inter-physician variability and improvement in quality of care facilitated by the adjustment and/or refinement of treatment recommendations concerning this patient population in (inter)national guidelines.

## Methods

### Design and collaboration

The RECOVER study is a comparative effectiveness study that prospectively includes patients with high-risk, non-metastatic PCa to compare treatment with robot assisted radical prostatectomy (RARP) versus EBRT combined with ADT. The study is executed by a cooperation of the Netherlands Comprehensive Cancer Organization (IKNL), the Dutch Association for Urology (NVU) and the Dutch Society of Radiotherapy and Oncology (NVRO). The study is performed in close collaboration with the Dutch Prostate Cancer Foundation (Prostaatkankerstichting [PKS]). Currently, 29 hospitals collaborating in four Dutch prostate cancer networks participate in the study, collectively covering 40% of all newly diagnosed prostate cancer patients in the Netherlands. ClinicalTrials.gov provides an up-to-date overview of all participating hospitals [17]. Healthcare providers from hospitals in a prostate cancer network discuss patient, tumor and other relevant characteristics in multidisciplinary team meetings (MDTMs) to achieve the most optimal treatment based on evidence-based guidelines and tailored to the patient. For this study, eligibility of a patient for treatment with both RARP and EBRT with ADT is discussed in these meetings. The participating networks are geographically distributed across the Netherlands and each network consists of at least one university hospital and several non-university teaching hospitals and general hospitals. In the Netherlands, surgical treatment of PCa is centralized in 14 hospitals that meet the minimum hospital volume norm of 100 RARP procedures per year [18]. Within each prostate cancer network, all RARP treatments are centralized in one hospital. Radiation therapy is centralized to 20 institutions across the Netherland and is performed in nine of the participating hospitals.

### Patient population

Patients with histologically confirmed high-risk, non-metastatic PCa diagnosed or treated in one of the participating hospitals are eligible for inclusion. Various (inter)national risk classifications and guidelines define high-risk PCa with subtle differences. In this study, high-risk, non-metastatic PCa is defined as cT3a-bN0M0 disease, and/or ISUP grade ≥ 4 and/or a PSA value at diagnosis above 20 ng/mL. Prostate cancer is staged according to the 8th edition of the Union for International Cancer Control (UICC) TNM classification with the exception that T-stage will be based on either digital rectal examination (DRE) or magnetic resonance imaging (MRI), whichever is highest [19, 20]. Patients must be aged 50 to 75 years, fit (WHO performance status 0–1) and eligible (i.e. no contra-indications) for both RARP and ERBT with ADT. Moreover, patients have to reside in the Netherlands and be able to read and understand Dutch language. Patients with histological PCa types other than adenocarcinoma and those that are diagnosed or treated in a hospital abroad are excluded. Patients treated with androgen receptor signaling inhibitor (ARSI)/androgen receptor targeted agents (ARTA) as part of the initial treatment plan are also excluded.

### Treatment

RARP may be part of a multimodal therapy with (neo)adjuvant ADT and/or adjuvant radiotherapy. A pelvic lymph node dissection (PLND) may be performed for staging purposes. The presence of positive lymph nodes (pN1) upon PLND is not a reason for exclusion and may be followed by adjuvant treatment e.g. lymph node irradiation and/or ADT.

Regarding EBRT, the study allows for dose-escalation using intensity modulated radiation therapy (IMRT), volumetric modulated arc therapy (VMAT) or stereotactic radiation. Dose-escalation is defined as a biologically effective dose (BED) converted to 2 Gy fractions (using a α/β ratio of 1.5) of at least 76 Gy. Both conventionally fractionated and hypofractionated regimens may be used and patients may receive an integrated boost to visible intraprostatic lesions, a low dose rate (LDR) brachytherapy boost or a high dose rate (HDR) brachytherapy boost. In addition, treatment with ADT should be given for a period of at least 6 months. Similar to radical prostatectomy, PLND may be performed for staging purposes and pN1 is no reason for exclusion.

### Study endpoints

The primary endpoints of the RECOVER study are functional outcomes and HRQoL 36 months after treatment initiation. These endpoints are measured with the validated Dutch versions of the Expanded Prostate Cancer Index Composite-26 (EPIC-26) [21] and the European Organization for Research and Treatment of Cancer Quality of Life Questionnaire-C30 (EORTC-QLQ-C30) [22]. We assume that the long-term effects of treatment, including the effects of ADT (patients eligible for inclusion generally receive ADT for 6 to 24 months), have stabilized 36 months after treatment initiation.

Secondary study endpoints are progression-free survival (PFS), distant metastasis-free survival (DMFS), cost and cost-effectiveness. Cost and cost-effectiveness will be evaluated 36 months after treatment initiation. PFS and DMFS are evaluated at 5 years after diagnosis.

### Patient inclusion

Eligible patients are informed about the study by their physician (or research nurse/nurse specialist) shortly after diagnosis. Study information is provided to the patient after which the patient has time to decide whether to participate in the study. Patient information is set up in such a way that it appeals to patients of diverse backgrounds. Patients willing to participate provide written informed consent and administrative data are entered in an online registration tool. Inclusion is finalized when the patient completes the first questionnaires before treatment initiation (baseline measurement). In some hospitals, the EPIC-26 and EORTC-QLQ-C30 are administered as part of the regular care. To minimize patient burden, these questionnaires are reused if possible.

### Data collection

#### Patient reported outcome measures (PROMs)

The EPIC-26 is an instrument developed and validated for the comprehensive assessment of HRQoL in men with PCa [21]. It is one of the best rated instruments for this purpose [23] and consists of 5 symptom domains: urinary incontinence, urinary irritative/obstructive, bowel, sexual, and hormonal. Questionnaire items are converted to domain scores between 0 and 100, with a higher score representing a better function. Threshold values for a clinically meaningful change (minimal clinically important difference [MCID]) have been determined for each EPIC-26 domain: 6 to 9 for urinary incontinence, 5 to 7 for urinary irritation, 4 to 6 for bowel function, 10 to 12 for sexual function and 4 to 6 for hormonal function [24].

The EORTC-QLQ-C30 is a widely used measurement instrument to assess HRQoL of cancer patients [22]. The questionnaire includes five functional domains (physical, role, cognitive, emotional and social), three symptom domains (fatigue, pain, nausea and vomiting) a global health/quality of life scale and several single-item measures. For each domain and single item measure, a score from 0 to 100 can be calculated. For the functional domains and global score, higher scores indicate a better quality of life. In contrast, for the symptom domains and single item measures, a higher score represents a higher level of symptomatology [22]. Musoro et al. have provided minimal important differences for within-group change and between-group change per EORTC QLQ-C30 scale for nine cancer types, amongst which prostate cancer [25].

In addition, patients are asked to complete an edited version of the self-administered comorbidity questionnaire (SCQ) and an adapted version of the Institute for Medical Technology Assessment Productivity Cost Questionnaire (iMTA PCQ). The SCQ is a generic questionnaire developed to assess common comorbidities which might impact an individual’s functioning. For each condition, the presence, severity and functional limitation is self-assessed [26]. We have extended the SCQ with conditions that are considered a (relative) contra-indication for RARP or EBRT, e.g. inflammatory bowel disease.

The iMTA PCQ is a standardized questionnaire developed to measure and value productivity loss. Productivity loss is measured in three modules being absenteeism, presenteeism and productivity loss of unpaid work [27]. The iMTA PCQ was slightly adapted in collaboration with an expert in health technology assessment by focusing questions regarding unpaid work on volunteer work only. Moreover, we reformulated some questions to make them more easily understandable for the patient. The iMTA PCQ is used to determine indirect non-medical costs.

Finally, information is collected regarding patient characteristics, such as living situation, alcohol and smoking behavior and education level, and used health resources for prostate-cancer related problems such as erectile or urinary complaints (e.g. urinary pads, catheter, medication). Information regarding used health resources is collected to determine healthcare costs. Table 1 presents the collected PROs at the various measurement moments.

The patient can complete either paper or web-based questionnaires based on their preference. Web-based questionnaires are collected by use of the Profiles Registry (Patient Reported Outcomes Following Initial treatment and Long term Evaluation). Profiles is specialized in collecting, processing and storing PROs of cancer patients [28] and all data are handled according to the General and Dutch Data Protection Act. Data from the PROFILES registry can be linked to the Netherlands Cancer Registry (NCR), which allows the merging of PROs and clinical data [29]. In order to achieve good response rates, a research assistant monitors the questionnaire response. Patients with incomplete questionnaires will be contacted and information will be complemented as far as possible.

**Table 1 Tab1:** Overview of the collection of patient reported outcomes in the RECOVER study at the subsequent measurement moments (baseline, T12 and T36)

Category	Included topics / patient reported outcome measures	Baseline	T12	T36
Patient characteristics	Age, length, height, living situation, alcohol and smoking behavior, education level, participatory decision making style	X		
Comorbidities	Adapted version of the SCQ	X	X	X
HRQOL and functional outcomes	EPIC-26 and EORTC-QLQ-C30	X	X	X
Treatment of PCa specific complaints / additional treatment information	Catheter, medication for lower urinary tract symptoms, pelvic floor physical therapy, surgery for urinary loss, erectile medication, use of vacuum pump erectile device, androgen deprivation therapy	X	X	X
Productivity loss	Adapted version of the iMTA PCQ	X	X	

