#### Clinical data

In addition to PROs, clinical data regarding patient and tumor characteristics, as well as treatment information, is needed to meet our research objectives. These data are extracted from the Netherlands Cancer Registry (NCR). Maintained by the Netherlands Comprehensive Cancer Organisation (IKNL), the NCR is a nationwide population-based registry that contains information on all newly diagnosed cancer patients in the Netherlands. Clinical data are retrieved from patients electronic health records in the hospitals by well-trained, independent data managers of the NCR. The standard data collection in the NCR is expanded for patients included in this study and includes patient characteristics (i.e. age, height, weight, comorbidities), tumor characteristics (i.e. TNM staging, PSA at diagnosis and Gleason grade on biopsy and prostatectomy if applicable), diagnostic procedures (i.e. imaging, biopsy technique, pelvic lymph node dissection) and treatment information for prostatectomy (i.e. nerve sparing procedure, positive margins, complications) and EBRT (i.e. type of radiotherapy, dose per fraction, integrated/brachytherapy boost, toxicity). In addition, data is collected on all post-treatment PSA measurements, disease progression, subsequent treatments and cause of death until 5 years after diagnosis. Vital status of all patients is updated annually by linkage to the personal records database (BRP) which contains data on the vital status, date of death and emigration status of all Dutch citizens.

Moreover, additional clinical data related to volumes of care are collected from the electronic health records to evaluate healthcare costs. In addition to the treatments for prostate cancer, these data include treatments for adverse events, consultations with medical specialists, hospitalizations and medication use.

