### Statistical analysis and sample size

Descriptive analyses will be used to provide insight in patient and clinical characteristics of the total study population and of both treatment groups. Mixed-effects models will be used to compare functional outcomes and HRQoL between the two treatment groups over time. Differences in functional outcomes and HRQoL between treatment modalities as measured by the EPIC-26 will be considered clinically meaningful if they are equivalent to or exceed the MCID and are statistically significant at the 0.05 level. The p-value maintained for statistical significance will be adjusted for multiple testing if appropriate. For the EORTC-QLQ-C30, the between-group anchor-based minimally important differences per scale as reported by Musoro et al. will be used to compare treatment groups over time. For scales for which no anchor-based estimates are available, distribution-based estimates will be used [25]. Due to the observational design of the study, we will adjust for confounding covariates associated with treatment with RARP versus EBRT (and ADT) using inverse probability of treatment weighting or the g-formula [30–33]. In case of missing values in covariates, multiple imputation procedures will be used [34, 35]. Competing risk survival analyses will be used to evaluate PFS and DMFS with the competing event being a non-PCa related death.

To evaluate incremental cost-effectiveness of EBRT combined with ADT versus RARP over a time horizon of 36 months, a cost-utility analysis (CUA) will be conducted both from a societal and a medical perspective. Costs are assessed by multiplying the voluminal with the unit prices. Utilities will be derived by means of a mapping algorithm from the EORTC QLQ-C30 at each time point. The derived utility will be used for the estimation of a quality adjusted life year (QALY) according to the trapezium rule. Incremental costs between treatments will be related to incremental QALYs in a cost-utility ratio (ICUR) to determine the additional costs that need to be spent to gain one QALY. Subsequently, a budget impact analysis (BIA) will be performed to predict the financial consequences related to the adaption and implementation of the favored strategy based on the cost-effectiveness analysis.

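### The societal cost-utility analysis covers 36 months, but productivity loss is scheduled for measurement only at baseline and month 12

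*Protocol article*

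**What the plan says.** The Statistical analysis and sample size section of the protocol article states that "over a time horizon of 36 months, a cost-utility analysis (CUA) will be conducted both from a societal and a medical perspective". The Study endpoints section agrees on timing: "Cost and cost-effectiveness will be evaluated 36 months after treatment initiation".

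The section on patient reported outcome measures gives the productivity questionnaire its role: "The iMTA PCQ is used to determine indirect non-medical costs". Table 1 sets out collection "at the subsequent measurement moments (baseline, T12 and T36". Its productivity row, "Adapted version of the iMTA PCQ", is marked at baseline and T12 and blank at T36. The rows for comorbidities, for EPIC-26 with EORTC-QLQ-C30, and for treatment of prostate-cancer complaints are marked at all three times. Patient characteristics are marked at baseline only.

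The Clinical data section adds that "additional clinical data related to volumes of care are collected from the electronic health records to evaluate healthcare costs". The items it lists are treatments, consultations, hospital stays and medication. None concerns work or volunteering.

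**The concern.** A societal perspective differs from a medical one here mainly through productivity costs, and the questionnaire is the only stated way of measuring them. If it stops at month 12, the societal ratio combines QALYs built from utilities at baseline, T12 and T36 with productivity costs observed no later than T12. The remaining two years must be left out or filled by assumption.

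The gap could matter to the comparison if productivity loss after month 12 differs between the arms. That is plausible. The article says ADT generally runs for 6 to 24 months and reports 6 to 36 months in current practice, so it can continue past T12 in the radiotherapy arm. Men are eligible from age 50, so some will be in paid work, and the adapted questionnaire also covers volunteer work. The article does not quantify any such difference.

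An analysis plan can state how to extrapolate, but it cannot recover answers that were never requested. That makes the collection schedule the place to act.

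**Working it through.** **Inputs from the article**
- Horizon of the societal analysis: 36 months (Statistical analysis and sample size).
- Last scheduled productivity measurement: month 12 (Table 1).
- Utilities: EORTC-QLQ-C30 at baseline, T12 and T36 (Table 1), combined by the trapezium rule (Statistical analysis and sample size).
- Start of accrual: February 2023; status date of the article: January 2025 (Start-up and patient accrual).

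The 36 months is a stated design value, so there is no calculated figure to reproduce.

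**Share of the horizon beyond the last measurement**

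(36 − 12) / 36 = 24 / 36 = 0.667, or 67%.

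With a T36 measurement this becomes (36 − 36) / 36 = 0. Months 12 to 36 would then lie between two measurements.

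**Is the empty cell real?** The patient-characteristics row shows its blanks in the same way, and the neighbouring rows keep their T36 mark. The blank therefore does not look like a fault in reading the table.

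**How far the result could depend on the unmeasured period (assumed values only).** Let the between-arm difference in productivity cost be 0 per month at baseline and 1 unit per month at T12, changing linearly between time points.
- Months 0 to 12: 12 × (0 + 1) / 2 = 6 units.
- Months 12 to 36: 24 × (1 + d) / 2 units, where d is the difference at T36.

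| d at T36 | Months 12–36 | 36-month total | Share after T12 |
|---|---|---|---|
| 1 | 24 | 30 | 80% |
| 0.5 | 18 | 24 | 75% |
| 0 | 12 | 18 | 67% |
| −0.5 | 6 | 12 | 50% |

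Counting nothing after T12 gives 6 units in every row. Carrying the T12 difference forward gives 6 + 24 × 1 = 30 units in every row. The same T12 data therefore yield anything from 6 to 30 units, depending on the rule chosen.

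Carrying forward is not an upper bound. If the difference is 0.5 at T12 and 1 at T36, the total is 12 × 0.5 / 2 + 24 × 1.5 / 2 = 3 + 18 = 21, against 3 + 24 × 0.5 = 15 carried forward.

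**How much ADT falls after T12 (assuming it starts at treatment initiation).** None of a 6-month course does, 12 / 24 = 50% of a 24-month course does, and 24 / 36 = 67% of a 36-month course does.

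**Timing.** February 2023 plus 36 months is February 2026. At the January 2025 status date the earliest patients were about 23 months from the start of accrual, so no T36 questionnaire had yet fallen due.

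**The case against.** The core facts are hard to dispute, but several stronger readings are tempting and the article does not support them.

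- **That the abstract contradicts Table 1.** The abstract says "Patient reported outcomes are collected before treatment initiation, 12 months and 36 months after treatment initiation and include the EORTC-QLQ-C30", and its list goes on to include "an adapted version of the iMTA Productivity Cost Questionnaire". A reader might infer that the questionnaire is promised at all three times. The same list also contains the patient-characteristics questions, which Table 1 collects at baseline only. The sentence summarises instruments and time points and does not give a schedule for each. It leaves open that Table 1 is in error, but is weak evidence of it.
- **That the relevant treatment falls mostly after T12.** For ADT, the shares above run from none to two thirds. For salvage radiotherapy after surgery, the article gives neither timing nor frequency. A difference between arms after T12 is plausible but not shown.
- **That two thirds of the productivity cost is missing.** The 67% is calendar time. The article gives no employment rate or size of productivity cost, and men up to 75 are eligible. It does not state the recall period of the adapted questionnaire either, so it is unknown how much of an interval one completed form covers.
- **That the budget-impact analysis would rest on unmeasured costs.** It follows the strategy favoured by the cost-effectiveness analysis, which is run from two perspectives. The article does not say that the societal one decides.

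Leaving the questionnaire out at T36 may also be a deliberate choice to limit burden, although no reason is given. An extrapolation rule may exist in a document not shown, so its absence here is not a fault. All of this limits the size of the point. None of it supplies productivity data after month 12.

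**Conclusion.** The point holds in limited form. As tabled, the schedule does not support the productivity component of a 36-month societal cost-utility ratio, because 24 of 36 months lie after the last measurement. The effect on the ratio cannot be sized from the article, and the unit-cost illustration shows only that the answer depends on the rule chosen for months 12 to 36.

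The reach is one cost component of one perspective of a secondary endpoint. QALYs, healthcare costs and the medical-perspective analysis keep their planned sources.

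The conclusion assumes that Table 1 is correct and that no source of productivity data exists beyond those named. If the questionnaire is in fact given at T36, what remains is an error in the table. This should be fixed, and the fix is easier before T36 questionnaires go out.

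**What to change.** Add the adapted productivity questionnaire to the T36 mailing and update Table 1. If it is already included at T36, correct Table 1 only. The cost is a minor amendment and a small extra burden for patients, who already receive a questionnaire at that time.

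For any patients without T36 productivity data, choose one of two courses before analysis:
- limit the societal analysis to 12 months and present the 36-month analysis from the medical perspective only; or
- keep the 36-month societal result, label its productivity component as extrapolated, and report sensitivity analyses from no productivity difference after T12 to the T12 difference carried forward. State that this range does not cover a difference that widens after T12.

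The first course gives up the long-horizon societal answer. The second keeps it at the price of an assumption that the study's own data cannot test for those patients.
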